## Abstract

**Background:**

Cancer-related fatigue is a common problem in persons with cancer, influencing health-related quality of life and causing a considerable challenge to society. Current evidence supports the beneficial effects of physical exercise in reducing fatigue, but the results across studies are not consistent, especially in terms of exercise intensity. It is also unclear whether use of behaviour change techniques can further increase exercise adherence and maintain physical activity behaviour. This study will investigate whether exercise intensity affects fatigue and health related quality of life in persons undergoing adjuvant cancer treatment. In addition, to examine effects of exercise intensity on mood disturbance, adherence to oncological treatment, adverse effects from treatment, activities of daily living after treatment completion and return to work, and behaviour change techniques effect on exercise adherence. We will also investigate whether exercise intensity influences inflammatory markers and cytokines, and whether gene expressions following training serve as mediators for the effects of exercise on fatigue and health related quality of life.

**Methods/design:**

Six hundred newly diagnosed persons with breast, colorectal or prostate cancer undergoing adjuvant therapy will be randomized in a 2 × 2 factorial design to following conditions; A) individually tailored low-to-moderate intensity exercise with or without behaviour change techniques or B) individually tailored high intensity exercise with or without behaviour change techniques. The training consists of both resistance and endurance exercise sessions under the guidance of trained coaches. The primary outcomes, fatigue and health related quality of life, are measured by self-reports. Secondary outcomes include fitness, mood disturbance, adherence to the cancer treatment, adverse effects, return to activities of daily living after completed treatment, return to work as well as inflammatory markers, cytokines and gene expression.

**Discussion:**

The study will contribute to our understanding of the value of exercise and exercise intensity in reducing fatigue and improving health related quality of life and, potentially, clinical outcomes. The value of behaviour change techniques in terms of adherence to and maintenance of physical exercise behaviour in persons with cancer will be evaluated.

**Trial registration:**

NCT02473003, October, 2014.

## Background

Cancer-related fatigue (CRF) is a multidimensional concept including physical, social, emotional, psychological and biological components experienced by persons treated for cancer. The biological mechanisms underlying CRF are not well understood [1]. CRF is reported in up to 90% of persons with cancer during adjuvant treatment with radiation therapy, chemotherapy and/or endocrine therapies [2, 3]. Clinically relevant levels of CRF have further been reported in approximately one-third of cancer survivors up to 6 years post-treatment [3, 4]. CRF has serious impact on the person’s health-related quality of life (HRQoL) [5, 6] and causes a considerable challenge to society in humans and economic terms [7]. Analysis shows that cancer-related mortality costs €75 billion in Europe in 2008 due to loss of productive life [8].

Systematic reviews emphasize the potential physical and psychosocial benefits from rehabilitation programs including physical exercise [9, 10]. Previous studies have suggested that exercise interventions in persons with cancer may be cost-effective [11–13]. At the same time, there are significant challenges associated with a change of lifestyle during and following cancer treatment [14, 15]. Studies that have evaluated the effectiveness of exercise interventions on CRF are not consistent with respect to exercise volume or intensity to be recommended [16, 17], highlighting the need for more research. Despite the growing body of evidence that exercise is beneficial to persons both during and after oncological treatment, persons still avoid exercise following the cancer diagnosis and reduce their physical activity levels [18, 19]. More research is needed regarding how to enable individuals to become and stay physically active [20] and which techniques [21] to use in order to facilitate this behavioural change [22].

The results of a meta-analysis indicate that physical exercise has a significant, clinically relevant positive effect on CRF [9, 16, 17, 23]. However, the results of randomized controlled trials are not consistent, and it is unclear which exercise intensity level is most appropriate and most efficacious for the management of CRF. From a methodological perspective, not all studies have had CRF as their primary outcome, and some studies were underpowered to detect a clinically relevant effect of exercise [9, 16, 17, 23].

From a bio-psychosocial perspective, exercise may comprise many different behaviours influenced by physical, psychological and contextual determinants of which some are amenable to change and others are not. Previous research among cancer populations has identified modifiable psychological determinants of physical exercise; the most salient being readiness to change, self-efficacy for exercise and perceived behavioural control [24, 25]. BCTs can be used to facilitate and encourage exercise behaviour change. This includes exploring motivational issues (e.g., pros and cons of exercise, readiness to change and self-efficacy for physical exercise) and using self-regulatory strategies (e.g. individual goal-setting, self-monitoring and analysing one’s own physical exercise behaviours, and developing plans for maintenance of exercise behaviour including generalization to various settings) [21, 26].

Endurance exercise has been shown to increase the level of anti-inflammatory cytokines, leading to a systematic lowering of pro-inflammatory cytokine response as part of the training adaptation and indicating a general anti-inflammatory effect of exercise [27]. There is some evidence that this anti-inflammatory response also depends on exercise intensity [27]. However, limited knowledge exists in persons with cancer [28]. In addition to anti-inflammatory responses, muscular expression of apoptotic and metabolic markers may also be relevant to the interplay between physical exercise and fatigue [29, 30]. While the causes of CRF among cancer survivors are not yet fully understood, decreased fitness, as well as immune and cytokine dysregulation have been suggested to play a role [9, 27]. Accumulating evidence also suggests that several pathways, including chronic inflammation, autonomic imbalance, HPA-axis dysfunction, and/or mitochondrial damage, could contribute to the disruption of normal neuronal function and result in CRF [28].

To summarize, there is evidence supporting the beneficial effects of exercise during adjuvant treatment in cancer persons, but the findings with regard to fatigue are inconsistent. Also, the mechanisms through which exercise reduces or prevents CRF are still not fully understood. There is still a need for large-scale and well-designed studies including persons at high risk of developing CRF during treatment [31]. In addition, more research is needed to determine the optimal level, intensity, and type of exercise, as well as how tailored BCTs and structured exercise regimes may contribute to increased exercise adherence and maintenance of physical activity behaviour throughout the cancer survivorship period [10]. Recently Barsewick et al. [1] highlighted the need to conduct longitudinal research on the interrelated bio-behavioural mechanisms underlying CRF, and to test mechanistic hypotheses within the context of CRF intervention research. Few studies have investigated the effects of physical exercise on genetic biomarkers and systemic inflammatory markers in cancer persons with and without CRF [31]. The present study aims to address many of these issues.

The *main aim* of this randomized controlled trial, Phys-Can, is to determine the effects of low-to-moderate and high intensity physical exercise with or without BCTs on CRF and HRQoL in persons with cancer, both during treatment and in the long-term, post-treatment survivorship period. Additionally, the trial will investigate the role of inflammation, cytokines and gene expression in the development and maintenance of CRF, as well as the cost-effectiveness of physical exercise programs during cancer treatment.

More specific, our objectives are to:Investigate the effects of low-to-moderate intensity exercise compared to high intensity exercise on person-reported outcomes (CRF as primary endpoint), chemotherapy/radiation completion rates, medical (oncology) adverse effects, physical activity and daily function, during adjuvant/curative treatment and at long-term-follow up. In addition, intervention effects on treatment tolerability and time to recurrence of cancer will be investigatedInvestigate if supplemental BCTs increase adherence to and the efficacy of a physical exercise intervention during and after adjuvant therapy.Explore the regulation of systematic inflammatory markers and muscular expression of cytokines in response to physical training and following training to investigate whether these serve as mediators for the effects on physical exercise on CRF and HRQoL.Evaluate the cost-effectiveness of physical exercise interventions for CRF from a societal perspective.

## Methods

The Phys-Can project is a randomized controlled trial with a preceding descriptive observational study to be used for comparisons.

The purpose of the observational study is to monitor how disease and treatment are associated with the person’s cardiorespiratory fitness, mental well-being, quality of life and patterns of physical activity over time. The same inclusion/exclusion criteria as in the Phys-Can intervention study were used. Persons with breast, colorectal and prostate cancer about to begin their neoadjuvant and/or adjuvant therapy in Uppsala, Linköping and Malmö/Lund were asked to participate. Inclusion started 15th of September 2014 and was terminated 28th of February 2015. A total of 95 persons were included. They followed the same intervals in terms of physical testing and self-report questionnaires as the persons in the Phys-Can intervention study, but were not participating in any exercise intervention. In addition to physical tests and person-reported outcomes, data from medical records in adjunction to adjuvant treatment and register data were collected to be used for health economic analyses.

Directly after completion of enrolment of persons in the observational study (15th of March 2015), the inclusion to the randomized controlled trial was started. Persons recently diagnosed with breast cancer, colorectal cancer or prostate cancer, scheduled for neoadjuvant chemotherapy (breast cancer) or endocrine therapy (prostate cancer), and/or adjuvant chemotherapy (breast- and colorectal cancer), adjuvant radiotherapy (breast cancer) and/or adjuvant endocrine therapy (breast- and prostate cancer) or radiotherapy with curative intent without additional endocrine therapy (prostate cancer) are invited to participate. Consecutive persons are recruited from Uppsala, Lund/Malmö and Linköping University hospitals. Persons who are not able to perform basic activities of daily living, who show cognitive disorders or severe emotional instability, who suffer from other disabling co-morbid conditions that might contraindicate physical exercise (e.g. heart failure, chronic obstructive pulmonary disease orthopaedic conditions or neurological disorders) are ineligible. All persons are assessed by a cancer specialist (oncologist or surgeon) regarding contraindications for high intensity exercise. Persons without contraindications receive a brief information sheet about the Phys-Can study, and are informed that there are no medical contraindications for them to participate. Next, eligible persons are contacted by one of the research staff and provided with more detailed information, both written and verbal, and are given the opportunity to ask questions. Those who agree to participate in the trial provide written informed consent.

The Phys-Can study was approved by the Regional Ethical Review Board in Uppsala, Sweden (Dnr 2014/249) and registered in ClinicalTrials.gov (TRN = NCT02473003, Oct, 2014).

### Design

The design is a 2×2 factorial design where participants are randomized to one of the following four groups (Fig. 1):individually tailored high intensity exercise with (H + BCTs) orwithout BCTs (H)individually tailored low-to-moderate intensity exercise with (LM + BCTs) orwithout BCTs (LM).

**Fig. 1 Fig1:**
[figure not shown]
Diagram of the participant flow through enrolment, baseline measurement, randomization, and follow-up. H = high intensity training; L = low intensity training; BCT = Behaviour Change Technique

The RCT is stratified and within each stratum randomization is carried out following a permuted block design with 8 participants per block. The defined strata are the three hospitals (Linköping, Lund and Uppsala) and three cancer sites yielding 9 strata. When all baseline measurements are finalized and reported in the project’s electronic case report form, the randomization is generated automatically in a web-portal (described below) of participants to an exercise group according to predefined strata (see above). The personnel in charge of recruitment then contact the participant with information on study condition and the first visit to the gym is scheduled.

All participants will exercise at least twice weekly for a period of 6 months under the guidance of trained coaches. Training intensity is 40–50% (LM) or 80–90% (H) of each individual’s heart rate reserve (Heart rate reserve = HRpeak-HRrest) and maximal muscle strength.

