### Sample size

The calculated sample size was based on detecting the main factorial effects of each factor on Multidimensional Fatigue Inventory (MFI) Physical Fatigue (PF) after completed intervention [32–34]. The target main effect size was determined to be 2, which according to Purcell et al. [35] is the minimal clinically important difference for the MFI-PF. We assumed that the standard deviation (SD) of PF was 5 in all four treatment arms, which is the SD reported in Purcell et al. [35], Hagelin et al. [36] and in an ongoing study within our research group (manuscript in preparation). Because three tests (two main and one interaction effect) were planned, the 5% significance level was adjusted using Bonferroni correction. In order to have 80% power to detect a main factorial effect of 2 under the null hypothesis of no effect, 67 individuals in each of the four treatment arms are needed, with a total sample size of 268 individuals.

Further adjustments of the sample size were necessary for several reasons. First, the sample size calculation was based on the assumption of no interaction effects. However, Montgomery et al. [29] argue that, if anticipating quantitative interactions, the trial should be powered to detect those effects. Interaction effects often are much smaller in size compared to the main effects. In clinical trials, it is therefore rare to have 80% power to detect the interaction effect. For instance, given the calculated sample size in the present study, the trial would have a power of only 22% to detect an interaction effect of 1. However, in the present study a possible interaction between the factors is of clinical interest. Thus, the original sample size was doubled, increasing the power to detect the interaction between to approximately 50%. Second, to account for missing data and drop-outs, the original sample size was increased further by 30%. Third, given that we include a baseline assessment, and assuming a moderate correlation (0.3) between the MFI-PF at baseline and follow-up assessments, the sample size can be reduced by approximately 10% [37]. Combining the above, we concluded that including approximately 150 individuals in each treatment arm, 600 individuals in total, should meet the statistical requirements of the trial.

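### A constant block size of 8 in nine hospital-by-cancer-site strata, with recruiting personnel passing on each condition, lets some coming allocations be predicted; the exposure is modest and cheap to reduce

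*Protocol article*

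**What the plan says.** The Design section describes a 2×2 factorial trial in which "participants are randomized to one of the following four groups". On the randomisation it says: "within each stratum randomization is carried out following a permuted block design with 8 participants per block". On stratification: "The defined strata are the three hospitals (Linköping, Lund and Uppsala) and three cancer sites yielding 9 strata". Each stratum therefore lies within one hospital and one cancer site.

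Allocation follows completion of baseline, when "the randomization is generated automatically in a web-portal". The same paragraph continues: "The personnel in charge of recruitment then contact the participant with information on study condition and the first visit to the gym is scheduled".

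Earlier, the Methods section describes the approach to candidates: "eligible persons are contacted by one of the research staff and provided with more detailed information, both written and verbal". Consent follows. That section also says that recruitment is consecutive and that a cancer specialist assesses everyone for contraindications to high intensity exercise before research staff make contact.

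The Sample size section plans "approximately 150 individuals in each treatment arm, 600 individuals in total". The Statistical analysis section includes baseline measurements in the model. It also plans an estimate from complete blocks only, as a check on the missing-at-random assumption.

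**The concern.** Automatic generation in a portal conceals the current draw. It does not stop someone from inferring the next draw from earlier ones when blocks have a single known length. Three features make that inference possible here. The block size is constant and published while the article describes recruitment in the present tense. Strata are local. The recruiting function learns each condition because it passes the condition on. No masking of participants or recruiters is described.

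Staff may have views on who would do well in the high intensity arms. A person who expects a particular arm next could encourage consent more or less strongly, or could bring forward or delay the reporting of baseline data, which triggers the draw. The main outcome is self-reported fatigue, so selection on motivation or expected tolerance could bear on the intensity contrast. The complete-block estimate would not help: its unbiasedness depends on who fills each place being unrelated to the arm attached to that place.

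**Working it through.** The article gives no figure for predictability, so there is none to reproduce.

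**Inputs.** Block size 8, four arms and 3 × 3 = 9 strata (Design); 600 participants with equal planned arms (Sample size). Equal arms imply 2 places per arm and 4 per intensity in each block. The number of possible blocks is 8!/(2!)⁴ = 2,520.

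**Assumptions for the ceiling.** The observer knows the block size and every earlier allocation in the stratum, nobody else in the stratum is awaiting randomisation, and all blocks are filled.

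**Certain arm.** The 8th place is always known. The 7th is known when the last two places hold the same arm, with probability 1/7. Average over the block: (1 + 1/7)/8 = 14.3%; 0.143 × 600 ≈ 86.

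**Certain intensity.** Places 8, 7, 6 and 5 are known with probability 1, 3/7, 1/7 and 1/35. Average: (1 + 3/7 + 1/7 + 1/35)/8 = 1.6/8 = 20.0%; 0.20 × 600 = 120.

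**Best guess.** The probability that the best guess is right, by place in the block:

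| Place | 1 | 2 | 3 | 4 | 5 | 6 | 7 | 8 | Mean |
|---|---|---|---|---|---|---|---|---|---|
| Arm | 0.250 | 0.286 | 0.333 | 0.400 | 0.443 | 0.476 | 0.571 | 1 | 47.0% |
| Intensity | 0.500 | 0.571 | 0.571 | 0.629 | 0.629 | 0.714 | 0.714 | 1 | 66.6% |

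Pure chance would give 25% and 50%.

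**People pending.** Steering has to happen before the draw. If k others in the stratum are ahead in the queue but not yet randomised, the guess at place j can use only j − 1 − k known allocations. The table therefore shifts right by k places, with the first k + 1 places at chance. For k = 1:
- certain arm = (1/7)/8 = 1.8%
- certain intensity = (3/7 + 1/7 + 1/35)/8 = 0.6/8 = 7.5%

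For k = 2, certain intensity = (1/7 + 1/35)/8 = 2.1%. Enumerating all 2,520 blocks confirms each row:

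| Others pending | Arm certain | Intensity certain | Best guess, arm | Best guess, intensity |
|---|---|---|---|---|
| 0 | 14.3% | 20.0% | 47.0% | 66.6% |
| 1 | 1.8% | 7.5% | 37.6% | 60.4% |
| 2 | 0% | 2.1% | 33.6% | 57.7% |
| 3 | 0% | 0.4% | 30.8% | 55.0% |

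The article does not give the number pending, so this is a range.

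**Effect of varying the block size.** Strata of 67 (600/9, equal strata assumed) were simulated with nobody pending and an observer who knows the possible sizes but not the current one:

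| Block sizes | Arm certain | Intensity certain | Best guess, arm | Best guess, intensity |
|---|---|---|---|---|
| 8 only | about 13.6% | about 19% | about 46% | about 66% |
| 4 and 8 | about 7% | about 10% | about 48% | about 67% |
| 4, 8 and 12 | about 3.3% | about 4.8% | about 45% | about 66% |

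The row for 8 only lies slightly below the exact figures because the last block in each stratum is unfilled. Varying the size removes certainty but does not improve the best-guess rate in any useful way.

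**Effect on the complete-block estimate.** Suppose 30% are missing, independently between people. A block is then fully observed with probability 0.7⁴ = 24.0% (size 4), 0.7⁸ = 5.8% (size 8) or 0.7¹² = 1.4% (size 12). If the 30% inflation in the Sample size section is read instead as a loss of 1 − 1/1.3 = 23%, the figures are 35.0%, 12.3% and 4.3%.

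**The case against.** The case on the other side is substantial, and most of it stands.

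- **The decision point is earlier than the draw.** Approach, information, consent and baseline testing all come before randomisation. One other person in the queue removes nearly all certainty about the arm. This stands, and it makes 86 and 120 of 600 ceilings.
- **Knowledge is assumed.** Nothing says that recruiters are told the block size or keep a tally, or that one individual both approaches candidates and passes on conditions for a whole stratum. Access to the list may be governed by a fuller document that is not shown. This stands, although the size is published and the notification task is stated outright.
- **There are safeguards.** The specialist check, consecutive recruitment and randomisation only after baseline narrow the room for steering. They do not govern how strongly someone is encouraged to consent or when baseline is reported.
- **Baseline is adjusted for.** A reader might infer that any imbalance would pass straight into the intensity effect. The Statistical analysis section does not support that, because measured baseline differences are at least partly taken up by the model. Adjustment would not remove unmeasured selection, for example on motivation. At the assumed baseline-to-follow-up correlation of 0.3, baseline physical fatigue explains about 0.3² = 9% of outcome variance.
- **The design is conventional.** Fixed blocks of 8 for four arms with portal allocation are not an error, and the article does not contradict itself here. This stands and sets the grade.

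**Conclusion.** The plan has a real but modest weakness. With a constant, published block size and recruiting personnel who learn each condition, some coming allocations can be predicted, so some selection bias can enter. The ceiling is 14.3% of allocations certain for the arm and 20.0% for intensity. With one or two people pending it falls to 1.8% or 0% and to 7.5% or 2.1%.

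The figures rest on 2 places per arm per block (inferred from equal planned arms) and on an observer who knows the block size and all earlier allocations in the stratum. A reader might go further and conclude that recruiters are steering enrolment, or that about 120 participants have a foreseeable intensity in practice. The article supports neither: it says nothing on tallies or on how many people await randomisation, and the size of any bias cannot be computed from it. This is a point to consider, not a required correction.

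**What to change.** Two changes, for blocks not yet opened:

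1. Have the portal draw each block size at random from 4 and 8, keep the sizes from site staff, and record the block identifier so that the complete-block analysis can still be run.
2. Have someone not involved in approaching or consenting candidates tell the participant the condition, so that recruiters do not see the running allocations. The assigned coach could do this, by phone or letter for participants without internet.

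The second change matters more. Varying the size roughly halves certainty but leaves the best guess about as good as before; withholding the running allocations is what reduces guessing. The Design section should be amended to match.

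Blocks of 12 would lower certainty further but are better avoided, because they would seldom be complete when data are missing and would weaken the planned complete-block estimate.

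The cost is a change to the portal's list and a reassigned notification task. Blocks of 4 are individually more predictable if their size becomes known: the last place is always certain, so 1/4 = 25% of allocations in such a block, against 14.3% in a block of 8. They also hold one person per arm, so the complete-block analysis would have to take its variance from differences between blocks.
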